## Abstract

**Background:**

Obese pregnant women are known to experience poorer pregnancy outcomes and are at higher risk of postnatal arteriosclerosis. Hence, weight control during and after pregnancy is important for reducing these risks. The objective of our planned randomized controlled trial is to evaluate whether the rate of change in body weight in obese women before pregnancy to 12 months postpartum would be lower with the use of an intervention consisting of Internet of Things (IoT) devices and mobile applications during pregnancy to 1 year postpartum compared to a non-intervention group.

**Methods:**

Women will be recruited during outpatient maternity checkups at four perinatal care institutions in Japan. We will recruit women at less than 30 weeks of gestation with a pre-pregnancy body mass index ≥ 25 kg/m^2^. The women will be randomly assigned to an intervention or non-intervention group. The intervention will involve using data (weight, body composition, activity, sleep) measured with IoT devices (weight and body composition monitor, activity, and sleep tracker), meal records, and photographs acquired using a mobile application to automatically generate advice, alongside the use of a mobile application to provide articles and videos related to obesity and pregnancy. The primary outcome will be the ratio of change in body weight (%) from pre-pregnancy to 12 months postpartum compared to before pregnancy.

**Discussion:**

This study will examine whether behavioral changes occurring during pregnancy, a period that provides a good opportunity to reexamine one's habits, lead to lifestyle improvements during the busy postpartum period. We aim to determine whether a lifestyle intervention that is initiated during pregnancy can suppress weight gain during pregnancy and encourage weight loss after delivery.

**Trial registration:**

UMIN: UMIN (University hospital Medical Information Network) 000,041,460. Resisted on 18^th^ August 2020. https://upload.umin.ac.jp/cgi-open-bin/ctr_e/ctr_view.cgi?recptno=R000047278

**Supplementary Information:**

The online version contains supplementary material available at 10.1186/s12884-021-03998-w.

## Background

The increase in the number of overweight/obese individuals with a body mass index (BMI) ≥ 25 kg/m^2^ worldwide [1] has led to an increased proportion of overweight/obese pregnant women [2]. In Asia, because of poorer health prognoses, a BMI ≥ 23 kg/m^2^ is generally considered overweight [3], while in Japan, a BMI ≥ 25 kg/m^2^ is considered obese; therefore, pregnant women whose pre-pregnancy BMI is ≥ 25 kg/m^2^ are considered obese [4].

In general, obese pregnant women are known to have poorer pregnancy outcomes than non-obese pregnant women [5]. In Japan, obese pregnant women are at high risk of miscarriage, preterm birth, stillbirth, and congenital anomalies and are reportedly at an increased risk of conditions such as pregnancy-induced hypertension, gestational diabetes, preterm birth, large-for-gestational-age infants, excessively large infants weighing ≥ 4 kg, venous thrombosis, cesarean section, and postnatal bleeding associated with cesarean Sect. [6, 7].

Obese women may also develop metabolic syndrome, comprising diabetes, hypertension, and dyslipidemia, and are at a high risk of arteriosclerotic diseases such as heart disease and cerebrovascular accidents, resulting in long-term postnatal health problems [8, 9]. If gestational diabetes or pregnancy-induced hypertension occurs during pregnancy, these risks are further elevated [10–12].

Weight control during and after pregnancy in obese pregnant women is important for reducing the risk of negative pregnancy outcomes and to avoid the occurrence of diseases after pregnancy in the long-term. In particular, excessive weight gain during pregnancy is associated with a high risk of postpartum weight retention (PPWR)[13], as well as the risk of being obese or overweight in the long term after pregnancy[14]. However, few reports have detailed on the longitudinal changes in postpartum weight in Japanese and other East Asian populations.

In Europe and the United States, numerous randomized controlled trials have conducted lifestyle interventions during and after pregnancy for obese pregnant women. Lifestyle interventions during pregnancy that combine diet and exercise have been shown to suppress weight gain during pregnancy [15]. Postpartum lifestyle interventions have shown promise in reducing PPWR [16]; however, many of these studies involved relatively short postpartum intervention periods of approximately 12 weeks. Further, lifestyle interventions for obese women initiated during pregnancy and continued into the postpartum period could affect weight gain during and after pregnancy, although the number of studies implementing such interventions has been limited [17–19]. In addition, while interventions using the Internet of Things (IoT) such as online services and mobile phones have been shown to help suppress weight gain during pregnancy in obese women [20], no studies have reported on the effectiveness of IoT-based interventions performed during and after pregnancy in obese Asian women.

The objective of the present study is to evaluate whether the weight change in obese women at 12 months postpartum compared to before pregnancy will become lower with an intervention utilizing IoT devices and mobile applications during pregnancy to 1 year postpartum compared to without an intervention. This paper describes the design and methods of the planned SpringMom study.

## Methods/Design

This protocol follows the SPIRIT guidelines [21]. SpringMom will be a multicenter randomized controlled trial in which participants will be randomly allocated to an intervention at each facility. The intervention will last until 1 year postpartum, and the participants will be observed until 2 years postpartum.

The enrollment period started in September 2020 and will end in June 2021, and the observation period started in September 2020 and will end in January 2024. Figure 1 shows the flow chart of the study procedures. This trial was approved by the ethics review board of the National Center for Child Health and Development, Tokyo, Japan.

**Fig. 1 Fig1:**
[figure not shown]
Flow chart of the study procedures

### Trial setting

The trial will be conducted at four perinatal institutions (National Center for Child Health and Development (Tokyo), Osaka Women’s and Children’s Hospital (Izumi City), Sato Hospital (Takasaki City), and Ehime Prefectural Central Hospital (Matsuyama City)). Participants are being recruited the physician at each site while they attend outpatient maternity checkups, and their written informed consent is obtained.

### Participants

Pregnant women who are examined at the abovementioned four institutions will be eligible for the study.

The inclusion criteria are as follows: < 30 weeks' pregnant when consent is providedPre-pregnancy BMI ≥ 25 kg/m^2^

The exclusion criteria are as follows: < 20 years old and never marriedNot a smartphone user or having a device with an operating system older than iOS 8.0 or Android 4.4Diagnosed with diabetes before pregnancy or overt diabetes during pregnancyWeighing ≥ 120 kg when consent is providedCannot communicate in JapaneseDeemed unsuitable for the trial by the physician in charge

### Allocation

Randomization will be conducted on the site level, not on the patient level. Every day during the enrollment period before starting recruitment, the trial secretariat will perform central allocation with a random number table to decide whether to enroll the participants in the intervention or non-intervention group at each site and, subsequently, will inform every site.

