### Blinding

According to the nature of the intervention, the participants and research coordinator at each site will not be blinded to the allocation. However, the physician at each site will be blinded to the allocation.

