### Intervention

The intervention will be initiated on the day consent is provided during pregnancy to 1 year postpartum. The IoT intervention for this trial is defined as (1) automatically generated advice based on data (weight, body composition, activity, sleep) measured using IoT devices and meal records and photographs recorded with a mobile application (Calo Mama Plus Pregnant woman Course®) and (2) provision of articles and videos related to obesity and pregnancy via a mobile application.

The following IoT devices will be distributed to all participants: body composition monitor and scale (HBF-227t, Omron Healthcare Inc., Tokyo) and fitness tracker (Fitbit Inspire®, Fitbit Inc., San Francisco, CA).

Participants in the intervention group will use a mobile application (Calo Mama Ninsanpu Plus®). The target weight 1 year postpartum has been set at 93% of the pre-pregnancy weight. Participants will monitor themselves daily to the extent possible using the IoT devices (weight and body composition monitor, activity, and sleep tracker) and by entering meal records and photographs into the mobile application.

The mobile application (Calo Mama Plus Ninsanpu Course®) has the following four functions: 

It automatically generates personalized advice based on conditions during and after pregnancy. Personalized advice is generated automatically based on data (weight, body composition, activity, and sleep) measured with the IoT devices and meal records and photographs recorded by the mobile application, alongside considering how far long in the pregnancy the participant is or the number of weeks postpartum.It provides articles based on the number of weeks of pregnancy or postpartum. The articles are delivered once or twice a week on themes that match the number of weeks of pregnancy or postpartum.It provides breastfeeding advice. After delivery, advice on breastfeeding is provided that reflects the breastfeeding status (number of times the participant recorded breastfeeding and amount of milk).It plots the body weight during pregnancy. Weight measurements during pregnancy are plotted on a graph and advice on weight changes based on the pre-pregnancy BMI is provided.

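### The day's arm is drawn per site before recruitment and sent to a site with an unblinded coordinator, with no concealment before consent, so selection into arms is possible

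*Protocol article*

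**What the plan says.** All references are to the protocol article.

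- **Allocation.** The unit is explicit: "Randomization will be conducted on the site level, not on the patient level". On timing, "Every day during the enrollment period before starting recruitment, the trial secretariat will perform central allocation with a random number table", which settles the group into which participants at each site are enrolled. The secretariat, "subsequently, will inform every site". The section does not name who at the site receives the message.
- **Blinding.** On one side, "the participants and research coordinator at each site will not be blinded to the allocation". On the other, "However, the physician at each site will be blinded to the allocation".
- **Trial setting.** "Participants are being recruited the physician at each site while they attend outpatient maternity checkups". The physician is thus the recruiter.
- **Participants.** The last exclusion criterion is the judgement of the physician in charge that a woman is unsuitable.
- **Intervention.** "The intervention will be initiated on the day consent is provided during pregnancy to 1 year postpartum". The same section puts routine maternity checkups at about 15 per pregnancy.
- **Analysis of primary outcome.** The model contains pre-pregnancy weight, time point, group and the time-by-group interaction. It has no term for site or day.

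**The concern.** Random generation of a sequence and concealment of the next assignment are separate safeguards. A central draw from a random number table provides the first. The procedure described here does not provide the second, because the assignment is made for the site and the day, and it leaves the secretariat before any individual woman has been registered.

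Anyone at the site who knows the day's arm can, deliberately or not, let it affect who is put forward, how the study is presented, or whether a woman is left for a later visit. Women who are keener to lose weight or more willing to use an app could then be over-represented on intervention days. Motivation plausibly predicts weight at 12 months, and the plan does not list it as a covariate. The resulting imbalance would appear as a treatment effect in the primary comparison, and no analysis could fully undo it.

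This is not a detail that a journal article leaves to the full protocol. The article states the procedure, and the procedure as stated releases the arm to the site without a concealment step.

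**Working it through.** **Step 1: who can know the arm, and when.**

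| Element | Section | Consequence |
|---|---|---|
| One arm per site per day | Allocation | All women recruited at a site on one day share an arm |
| Drawn before recruitment, then sent to sites | Allocation | The arm is fixed before any woman that day is approached; notice before the first approach is the natural reading |
| Coordinator unblinded | Blinding | At least one member of site staff can know the arm in advance |
| Physician blinded | Blinding | On paper, the recruiter does not know the arm |
| Physician recruits and judges suitability | Trial setting; Participants | The physician's blinding would have to hold at approach and at eligibility |
| Intervention starts on the day of consent | Intervention | The first enrolment of a day can reveal the arm for later women that day |

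For a person who has been told the day's arm, the next woman's assignment is predictable with probability 1.0. Under concealed 1:1 individual allocation it would be 0.5.

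**Step 2: reproduce the plan's sample size.** Inputs from the Sample size section: difference −2% − (−5%) = 3 percentage points, SD 8%, two-sided alpha 0.05, power 80%.

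- Normal approximation: n = 2 × (1.960 + 0.842)² × 8² / 3² ≈ 111.6, so 112 per arm and 224 in total.
- Two-sample t-test: 112.6, so 113 per arm and 226 in total, which is the stated figure.

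The sample-size arithmetic is sound and does not bear on concealment.

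**Step 3: what a selection shift would do.** The documents give no size for the bias. Assume that selection improves the intervention arm's expected 12-month weight change by b percentage points, with no true effect, equal arms and independent women.

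- SE = 8 × √(2/113) = 1.064.
- P(reject) = Φ(b/SE − 1.96) + Φ(−b/SE − 1.96).

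| Assumed b (points) | b in SD units (b/8) | Share of the 3-point effect | b/SE | Two-sided rejection rate |
|---|---|---|---|---|
| 0 | 0 | 0% | 0 | 5% |
| 0.5 | 0.06 | 17% | 0.47 | 7.6% |
| 0.8 | 0.10 | 27% | 0.75 | about 12% |
| 1.0 | 0.125 | 33% | 0.94 | 15.6% |
| 1.6 | 0.20 | 53% | 1.50 | about 32% |

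Taking the 270 registrations less 20% instead gives 216, or 108 per arm, with SE = 8 × √(2/108) = 1.089. The rates for 0.8 and 1.6 points are then about 11% and 31%, so the choice hardly matters.

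**Step 4: how often one enrolment could unmask another on the same day.** Assume 20 clinic days a month. Over the 10-month enrolment period (Methods/Design) there are 4 × 10 × 20 = 800 site-days, or 270/800 = 0.34 women per site-day. Under a Poisson assumption, about 16% of site-days with any enrolment have a second woman. With the 5-month registration period in the Sample size section there are 400 site-days, or 0.675 women per site-day, and the share is about 30%. This route exists but is limited. The coordinator's advance knowledge is the stronger one.

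**The case against.** The strongest defence is the stated blinding of the physician. Recruitment and the discretionary exclusion both belong to the physician, so on paper the person who approaches women and judges suitability is unaware of the arm. A reader might infer that the arm is fully known to everyone at approach, eligibility judgement and consent. The documents do not support that. They do not say that the physician is told, they do not name the recipient at the site, and they do not say whether a woman knows her arm when she consents. The words about timing also attach to the draw. Notice to the sites follows, and its arrival before the first approach is the natural reading rather than an explicit statement.

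Three further limits are fair.

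- Putting a woman off to another visit can avoid today's arm, but the future day's arm has not yet been drawn, so she cannot be booked into a chosen one.
- A reader might see a contradiction in Methods/Design, where "participants will be randomly allocated to an intervention at each facility". That is thin, because the phrase can loosely describe site-day allocation.
- The size of any bias is assumed, in one direction only.

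What remains is that the coordinator can know the arm in advance, no concealment step is described, and the physician's blinding is asserted without a mechanism in a setting where the site has been informed. Even perfect physician blinding would leave the coordinator's influence on who is put forward and how the study is presented.

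**Conclusion.** The concern stands in this form: the stated procedure fixes one arm per site-day before recruitment and releases it to a site with an unblinded coordinator, without concealment until eligibility and consent are recorded. Selection into arms is therefore possible, and adjustment for pre-pregnancy weight would not remove it. Trial setting, Allocation and Blinding have to be reconciled.

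Confidence is high that the coordinator can know the arm beforehand, and moderate that the physician can infer it. Nothing in the documents shows that selection occurred. The type I error of about 12% to 32% is an illustration that depends on an assumed shift of 0.8 to 1.6 points, not an estimate. The point should be settled before the primary result is interpreted as a randomised comparison.

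**What to change.** **Remaining enrolment.** Confirm eligibility, record consent and register the woman with the secretariat. Only then draw and release her individual allocation, stratified by site, with concealed blocks of varying size. Rewrite Allocation to match, and make Trial setting and Blinding consistent with it: who is told, when, and how the physician is kept unaware.

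**Women already enrolled by site-day.** Enrolment began in September 2020 and was due to end in June 2021, so this may be the larger part of the remedy.

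- Describe the allocation as site-day.
- Keep the site-day identifier and account for it in the analysis.
- Report the numbers eligible, approached, excluded and consented by arm of the day. Differences between arms would be a warning sign of selection.
- Run a sensitivity analysis by allocation method, and state that it will be imprecise because the 270 women are split between methods.

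**Cost.** A protocol amendment and one request to the secretariat per woman. The secretariat already allocates centrally every day. The formula sample size for individually allocated women stays at 226. The downsides are that two allocation methods must be described, and app set-up cannot be prepared before consent.

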### Blinding

According to the nature of the intervention, the participants and research coordinator at each site will not be blinded to the allocation. However, the physician at each site will be blinded to the allocation.

### Intervention

The intervention will be initiated on the day consent is provided during pregnancy to 1 year postpartum. The IoT intervention for this trial is defined as (1) automatically generated advice based on data (weight, body composition, activity, sleep) measured using IoT devices and meal records and photographs recorded with a mobile application (Calo Mama Plus Pregnant woman Course®) and (2) provision of articles and videos related to obesity and pregnancy via a mobile application.

The following IoT devices will be distributed to all participants: body composition monitor and scale (HBF-227t, Omron Healthcare Inc., Tokyo) and fitness tracker (Fitbit Inspire®, Fitbit Inc., San Francisco, CA).

Participants in the intervention group will use a mobile application (Calo Mama Ninsanpu Plus®). The target weight 1 year postpartum has been set at 93% of the pre-pregnancy weight. Participants will monitor themselves daily to the extent possible using the IoT devices (weight and body composition monitor, activity, and sleep tracker) and by entering meal records and photographs into the mobile application.

The mobile application (Calo Mama Plus Ninsanpu Course®) has the following four functions: 

It automatically generates personalized advice based on conditions during and after pregnancy. Personalized advice is generated automatically based on data (weight, body composition, activity, and sleep) measured with the IoT devices and meal records and photographs recorded by the mobile application, alongside considering how far long in the pregnancy the participant is or the number of weeks postpartum.It provides articles based on the number of weeks of pregnancy or postpartum. The articles are delivered once or twice a week on themes that match the number of weeks of pregnancy or postpartum.It provides breastfeeding advice. After delivery, advice on breastfeeding is provided that reflects the breastfeeding status (number of times the participant recorded breastfeeding and amount of milk).It plots the body weight during pregnancy. Weight measurements during pregnancy are plotted on a graph and advice on weight changes based on the pre-pregnancy BMI is provided.

In addition, episodes from "Hana-chan's best chance for pregnancy and postpartum weight loss," a manga comic that discusses pregnancy and obesity, are automatically sent to the mobile application. The story consists of 10 episodes, with episodes 1–7 sent during pregnancy and episodes 8–10 sent after delivery (Supplementary Table 1).

The mobile application for pregnancy will be used during pregnancy until delivery; afterward, the participants will switch to a postpartum application, with the intervention resuming at 6 weeks postpartum and continuing until 1 year postpartum.

Participants in the non-intervention group will undergo regular maternity checkups, receive health guidance (usually until 1 month postpartum), and be provided with medical care covered by health insurance as needed. In Japan, women usually undergo maternity checkups approximately 15 times roughly throughout 10 months of pregnancy. The IoT devices (weight and body composition monitor, activity, and sleep tracker) must be worn when the data are collected (start of the study and at 1, 6, 12, and 24 months postpartum). The articles provided to the intervention group will also be available on a website.

During the study period, the research coordinator at each site will ask the participants in the intervention group if there is any inconvenience in using the device and mobile application. In both groups, useful information on infants will be regularly sent by e-mail after delivery to prevent dropouts.

Figure 2 shows the study timeline for intervention and data collection.

